### Data monitoring and confidentiality

2.13

Researchers will be trained in a unified way before the study to ensure it is performed correctly. Data will be locked in the airtight cabinet and will be entered and checked by double entry into the database established by data administrator using Excel 2019 edition (Microsoft Corporation, Redmond, WA) for management after completion of the study. An independent statistician will analyze the data while the procedure will be monitored by a third individual. The data of the patients involved in the trial will be confidential and will be used only by scientific research institutes. The publication or reporting of any research findings will not reveal the individual identity.

### Planned statistical analysis

2.14

Continuous variables will be described as the mean ± standard deviation, median, or interquartile range. The number of cases, frequency, the rate, and the constituent ratio will be described by categorical variables. Variance analysis will be used for continuous variables in the baseline data having normal distribution and same variance. Wilcoxon rank sum test or Kruskal–Wallis H test will be used for the comparison of differences between groups that are not normally distributed or have uneven variance. Categorical variables will be tested by *χ*^2^ test or Fisher exact test. Wilcoxon rank sum test or Kruskal–Wallis H test will be used for the number of CSBM per week in primary outcome. *χ*^2^ test or Fisher exact test will be used for percent improvement of each symptom scale score in secondary outcome indicators. The result of 48-hour GITT will be analyzed using *χ*^2^ or Fisher test. Wilcoxon rank sum test or Kruskal–Wallis H test will be used for measurement data in HRAM, while *χ*^2^ test or Fisher exact test will be used for counting data. Safety, dietary quality, compliance indicators will be tested by *χ*^2^ test or Fisher exact test. Complying with the intent-to-treat and per-protocol principle, all data of the patients randomized and at least 1 assessment (include baseline assessment) will be analyzed. For dropouts and terminations, their missing data will be obtained by last-observation-carried-forward method. All statistical analyses will be performed by SPSS23 software (IBM, Chicago, IL), and *P* value <.5 will be considered statistically significant.

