### Study objective and hypotheses

2.1

This exploratory research project aims to study the effectiveness of QJTCF and light vegetarian therapy for functional constipation and the changes of short-chain fatty acids in feces before and after treatment.

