### Study design

2.2

The protocol was drafted using the SPIRIT guidelines and the results will be reported following the checklist of the Consolidated Standards of Reporting Trials statement (see Supplementary Table 1). All participants will be informed of the purpose of the study and obtain their informed consent before participating in this parallel group study. According to the inclusion and exclusion criteria, a total of 90 patients with functional constipation are expected to be recruited. Then they were randomly assigned to the Chinese medicine group (group A), placebo + diet group (group B), Chinese medicine + diet group (group C) at the ratio of 1: 1: 1. The patient filled out the case report form (CRF) after confirming enrollment, and the researchers recorded the patient's symptoms, bowel movements, etc., on day 14 (phone follow-up) and day 28. Interventions were provided to subjects based on the enrollment number, but neither the patient nor the investigator knew whether the patient was receiving drug or placebo. The entire study design is shown in the figure (see Fig. 1). A SPIRIT figure for the schedule of enrolment, interventions, and assessments is also presented (see Fig. 2).

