### Sample size

2.5

Because there is still insufficient clinical evidence, this study is a small sample exploratory study with a total sample size of 90 people (each treatment group has 30 samples).

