#### Baseline information

2.11.1

Baseline information will include demographic data and clinical data from the participants. Demographic data includes gender, age, height, weight, nationality, occupation, and education level, etc. Clinical data includes past medical history, drug allergy history, the history of medications used to treat or induce constipation, dietary habits in the past year (see Supplementary Table 1), the primary outcome, and secondary outcomes.

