#### Primary outcome

2.11.2

The number of CSBM per week is the primary outcome. It is effective when the number before the intervention subtracted from the number after the intervention is more than or equal to 1.

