## Discussion

3

FC is a common disease of the digestive system and is characterized by persistent or recurrent difficulty in defecation. Constipation can cause digestive symptoms such as loss of appetite, abdominal distension, hemorrhoids, and colon polyps. It can also lead to cardiovascular and cerebrovascular diseases,^[18–20]^ kidney diseases,^[21,22]^ and even sudden death. At present, traditional Chinese and Western medicines used to treat functional constipation can only temporarily improve constipation. Constipation can easily recur after stopping the medication. Some traditional Chinese medicines also cause damage to the intestinal tract (melanosis coli).^[23,24]^ Long-term improvement of constipation can be achieved through the management of patients’ cognitive behavioral patterns. Studies have shown that dietary fiber supplementation can improve chronic constipation, but there is no intervention study on constipation with a vegan diet.^[25–27]^ In clinical practice, maintenance of FC improvement has been observed in patients who persist in LVD for a period of time without any drug use. TCM is a national medicine in China.^[28,29]^ It has been caring for the health of Chinese people from ancient times to present. TCM has mature experience in the treatment of constipation. Qing Jiang Tiao Chang Fang is a safe and effective prescription. However, these are only the results of clinical observations and need to be scientifically validated in clinical trials. This RCT aims to clarify the efficacy and safety of LVD and QJTCF on FC by designing rigorous trials. The results of the study can provide more evidence for dietary intervention and TCM intervention on FC, and to some extent, clarify the complementary effect of diet on drugs. There are still some limitations in this study:

1.Dietary intervention is a cognitive behavioral therapy, and there are many objective factors that will hinder the practice of light vegetarian diet and affect the experimental results.2.The experiment explored the metabolic effects of vegetarian diet and traditional Chinese medicine on fecal short-chain fatty acids, but no other metabolites were studied.3.The current study belongs to exploratory study with small sample size.

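### The primary test on weekly CSBM carries no baseline term although baseline is collected and benefit is judged by change, and a Kruskal-Wallis result alone cannot say which treatment works

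*Protocol article*

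**What the plan says.** Under Planned statistical analysis (2.14), the only test assigned by name to the primary outcome is a Wilcoxon rank sum or Kruskal–Wallis "H test will be used for the number of CSBM per week in primary outcome". The sentence mentions no covariate. It does not say whether the value ranked is the post-treatment figure or the change, and it does not say which groups are compared.

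Three other sections bear on it:

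- Primary outcome (2.11.2) first says "The number of CSBM per week is the primary outcome" and then adds a success rule: "It is effective when the number before the intervention subtracted from the number after the intervention is more than or equal to 1".
- Baseline information (2.11.1) lists, among the clinical data taken at entry, "dietary habits in the past year (see Supplementary Table 1), the primary outcome, and secondary outcomes". A baseline value of the primary outcome is therefore planned.
- Study objective and hypotheses (2.1) says the project "aims to study the effectiveness of QJTCF and light vegetarian therapy for functional constipation". The Discussion repeats the double aim: "This RCT aims to clarify the efficacy and safety of LVD and QJTCF on FC by designing rigorous trials".

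The arms (2.2) are "Chinese medicine group (group A), placebo + diet group (group B), Chinese medicine + diet group (group C) at the ratio of 1: 1: 1". Sample size (2.5) gives a "total sample size of 90 people (each treatment group has 30 samples", with no power basis.

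**The concern.** The success rule measures each patient against their own starting point, and that starting point is recorded, but the named test does not use it as a covariate. In a trial of 30 per arm, a baseline measure of the outcome is the cheapest source of precision available, and the plan as written leaves it unused.

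The second part concerns interpretation. The objective names two treatments. Kruskal–Wallis across three arms asks only whether any arm differs from any other. If that were the only primary result, the trial could report significance without answering for either the formula or the diet. Of the three pairwise comparisons, C versus B changes the formula with diet held fixed, C versus A changes the diet with formula held fixed, and A versus B changes both at once.

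**Working it through.** **Inputs from the article.** 30 patients per arm and 3 × 30 = 90, which agrees with the stated total. Arms A (formula), B (placebo + diet), C (formula + diet). Baseline CSBM collected. No effect size, SD, power or correlation is given, so there is no plan figure to reproduce.

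**Assumptions for illustration.** Baseline-to-follow-up correlation r = 0.3, 0.5, 0.7; two-sided alpha 0.05; normal outcomes; arm means A = 0.3, B = 0, C = 0.6 in SD units, so C − B = 0.6 and C − A = 0.3.

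**Step 1: variance.** Let 1 be the variance of the post-treatment value. A change score has variance 2(1 − r). The baseline-adjusted value has variance 1 − r². Equivalent size per arm is 30 / (1 − r²).

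| r | post-treatment only | change | adjusted | 30 per arm acts like |
|---|---|---|---|---|
| 0.3 | 1 | 1.40 | 0.91 | 33 |
| 0.5 | 1 | 1.00 | 0.75 | 40 |
| 0.7 | 1 | 0.60 | 0.51 | 59 |

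Adjustment has the smallest variance in every row, so it improves on both readings of the planned test: ranks of post-treatment values or ranks of changes. A plain change score is worse than ignoring baseline when r is below 0.5.

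**Step 2: power for C − B, by hand at r = 0.5.** Power ≈ Φ(d·√(n/2) / √(1 − r²) − 1.96).

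- Unadjusted: 0.6 × √15 = 2.32; Φ(2.32 − 1.96) = 0.64.
- Adjusted: 2.32 / √0.75 = 2.68; Φ(2.68 − 1.96) = 0.77.
- C − A adjusted: 0.3 × √15 / √0.75 = 1.34; Φ(1.34 − 1.96) = 0.27.

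**Step 3: simulation of the same scenario,** which allows for estimated variances and for Holm:

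| Analysis | r = 0.3 | r = 0.5 | r = 0.7 |
|---|---|---|---|
| Kruskal–Wallis, three arms | about 50% | about 49% | about 50% |
| Wilcoxon, C versus B | about 60% | about 60% | about 60% |
| t-test, C − B | about 63% | about 63% | about 63% |
| Baseline-adjusted C − B | 68% | 75% | 89% |
| Baseline-adjusted C − B, Holm over two contrasts | 58% | 65% | 83% |
| Baseline-adjusted C − A, no Holm | 23% | 26% | 36% |

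The like-for-like gain from adjustment at r = 0.5 is 75 − 63 = 12 points. Setting 75% against the Kruskal–Wallis figure would compare two different hypotheses.

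**Step 4: what an omnibus result can say.** In a separate simulation (SD 2, r = 0.5, 30 per arm, true effect 1 CSBM per week), Kruskal–Wallis rejects 46% of the time when only the formula works and 45% when only the diet works. The result does not separate the two cases. With no rule for the three pairwise Wilcoxon tests, the chance of at least one false positive at 0.05 each is about 11%.

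**The case against.** Much can be said for the plan, and most of it stands.

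- **Validity.** Randomisation makes the unadjusted rank test valid. A reader might infer that omitting baseline biases the comparison; it does not.
- **Ambiguity.** The text does not say that post-treatment values are ranked. Because the success rule is an after-minus-before difference, changes may be meant. It would be too strong to say that the plan certainly ignores baseline. What stands is that no baseline term is named, and step 1 shows that adjustment is more precise under either reading.
- **Pairwise tests.** The analysis section also names Wilcoxon rank sum, a two-group test, so pairwise comparisons are foreseen. The plan is not omnibus-only, and a condensed article may leave the list of contrasts and estimates to a fuller document.
- **Responder rule.** The general sentence giving χ² or Fisher for categorical variables can cover a yes/no responder. The rule is not without a test; it is only not tied to the primary outcome by name.
- **Within-arm claims.** Because no arm is free of both treatments, one might infer that the trial will claim efficacy from one arm's own response rate. The article plans no such claim.
- **Clean isolation.** C − B and C − A do not isolate the treatments perfectly. The placebo contains formula powder at 5 of 110 parts, or 4.5% (Intervention, 2.7). The diet is open-label, and diet patients are urged by phone to keep to it.
- **Size of gain.** The correlation is unknown. The diary is described for the treatment period only, so baseline CSBM may rest on recall, which could lower r.
- **Exploratory status.** The article repeatedly calls the study small and exploratory, so strict multiplicity control is an option and not an obligation.

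None of this explains leaving a collected baseline out of the primary analysis.

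**Conclusion.** The point holds in a limited form. The primary outcome is assigned a rank test with no baseline term, although the article collects baseline CSBM and judges benefit by change from it. The loss is precision: 9%, 25% or 49% of the variance at assumed r of 0.3, 0.5 or 0.7. In the assumed scenario this is worth about 12 power points for C − B at r = 0.5. If Holm is then applied over two contrasts, most of that gain is spent (65% against 63% unadjusted and uncorrected), and C − A stays near 26% even without Holm. Adjustment therefore does not make 90 patients adequate for both questions.

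Separately, a Kruskal–Wallis result alone cannot attribute an effect to the formula or to the diet. The variance factors need only the correlation, with a linear relation and equal spread. The power figures also rest on assumed effects and normal data, while CSBM is a weekly count, so they are illustrative. All take alpha as 0.05; the threshold printed in the article is .5, which is a different matter.

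**What to change.** Reword Planned statistical analysis as follows.

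1. Primary analysis: end-of-treatment CSBM per week, adjusted for baseline CSBM, by ANCOVA, or by rank ANCOVA if the data are skewed.
2. Report two contrasts, each with a 95% confidence interval: C − B, described as full formula against placebo containing 5/110 formula powder, both on the diet; and C − A, described as open-label diet with coaching added to the formula.
3. State either a Holm rule for the two contrasts or that both are exploratory.
4. Report A − B as descriptive, because it changes both treatments.
5. Keep the response rule of at least 1 CSBM per week as a supportive between-group comparison, and name its test.

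The cost is wording only. Baseline and follow-up CSBM are already in the data plan, and no visit, measurement or patient is added. The change should be fixed before the third party breaks the blind.

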#### Secondary outcomes

2.11.3

Constipation-related symptom rating scale: The scale for constipation-related symptoms is used for investigating the degree and frequency of symptoms mentioned in Roman IV diagnostic criteria for FC. The degree of discomfort is assessed by visual analog scale, in which 0 represents no discomfort and 10 represents very strong discomfort. The final scores are obtained with the multiplication of the 2 and then divided by the average number of defecations per week (see Supplementary Table 2). Percent improvement will be calculated as follows: 

Recovery means symptoms disappeared; Marked improvement means percent improvement is more than or equal to 80%; Progress means percent improvement is more than or equal to 50% but less than 80%; Ineffective means percent improvement is less than 50%.

Traditional Chinese medicine syndrome scale (TCMSS): The TCMSS is established by collecting information about effects of relevant syndromes of TCM constipation, which are assigned 0, 1, 2, and 3 points representing normal, mild, moderate, and severe degrees, respectively. Normal refers to the absence of this syndrome, mild refers to a slight impact on life, moderate means a significant impact on life, and severe refers to the serious impact on life (see Supplementary Table 3). Nimodipine method is used for evaluating the effects of relevant syndromes of TCM constipation. 

Symptoms, signs disappeared or basically disappeared and syndrome integral reduced more than or equal to 95% is considered clinical cure; Significantly effective means that symptoms, signs significantly have improved, and syndrome integral has reduced more than or equal to 70%; Effective means that symptoms, signs have improved and syndrome integral has reduced more than or equal to 30%; Ineffective means that symptoms, signs have no improved or have even aggravated and syndrome score has reduced less than 30%.

Forty-eight hours GITT: 48-hour GITT is a simple method for evaluating the function of gastrointestinal motility. The barium residue rate is the ratio of the number of barium remaining in the body 48 hours after swallowing 20 barium bars with a standard meal. Higher residue rate indicates the worse gastrointestinal transport function. The parameters include barium excretion rate after 48 hours, residue rate above rectosigmoid colon and residue rate within rectosigmoid colon. The barium excretion rate in normal people is more than or equal to 90%.

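### Chi-square or Fisher tests for 48-hour transit rates and graded percent improvement waste power, and leave two of the three transit rates without a defined table

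*Protocol article*

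**What the plan says.** Section 2.11.3 (Secondary outcomes) defines the residue rate as "the ratio of the number of barium remaining in the body 48 hours after swallowing 20 barium bars with a standard meal". It then lists three quantities: "The parameters include barium excretion rate after 48 hours, residue rate above rectosigmoid colon and residue rate within rectosigmoid colon". One reference value is given: "The barium excretion rate in normal people is more than or equal to 90" per cent. Neither residue rate has a limit.

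The same section grades percent improvement on the constipation symptom scale into four ordered classes. The lower two read "Progress means percent improvement is more than or equal to 50% but less than 80%; Ineffective means percent improvement is less than 50" per cent; above them stand marked improvement (80% or more) and recovery. The traditional Chinese medicine syndrome scale (TCMSS) also has four ordered grades, with limits at 95%, 70% and 30% reduction. For example, "Effective means that symptoms, signs have improved and syndrome integral has reduced more than or equal to 30" per cent.

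Section 2.14 (Planned statistical analysis) states "The result of 48-hour GITT will be analyzed using" chi-square or Fisher, without naming the unit counted or a cut. It also states that the chi-square "test or Fisher exact test will be used for percent improvement of each symptom scale score in secondary outcome indicators". In that same section, measurement data from high-resolution anorectal manometry (HRAM) and the weekly number of complete spontaneous bowel movements (the primary outcome) go to Wilcoxon or Kruskal-Wallis, and chi-square is kept for the counting data of HRAM.

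**The concern.** A transit rate out of 20 markers is one quantitative value per patient, of the same kind as the HRAM measurements that the plan gives to rank tests. A chi-square test needs counts of independent units in categories, so the rate must first be turned into a category. For excretion the 90% limit offers one. For the two residue rates the article offers none.

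Percent improvement is a per-patient percentage placed in ordered grades. An unordered chi-square ignores that order, and grading has already discarded most of the magnitude. With 30 patients per group, what is at stake is mainly power on secondary outcomes, and for the residue rates whether the stated test can be carried out at patient level at all.

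**Working it through.** The article gives no effect size, standard deviation or power for these outcomes, so there is no stated figure to reproduce. Section 2.5 gives 90 patients, 30 per group (3 × 30 = 90).

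**Inputs from the article:** 30 per arm; 20 markers per patient; normal excretion at least 90%, i.e. 18 of 20; grade limits for the symptom scale.

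**Assumed inputs:** two-sided 5% level; correlation between markers within a patient (ICC) of 0.1 to 0.5; mean excretion 60% v 78%; percent improvement 40 v 65 with SD 35. Power comes from simulated trials with beta-binomial markers and percentages limited to 100.

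**1. Excretion rate, patient-level split at 90%, two arms**
- ICC 0.3: chi-square about 60%, rank test on the rate about 76%, a gap of 76 − 60 = 16 points.
- Same means: the gap is about 21 points at ICC 0.1 and about 12 at ICC 0.5.
- Smaller difference and higher correlation (60% v 75%, ICC 0.6): the gap is about 6 points.

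Three-arm check with means 50/50/70%: 60% v 80% at ICC 0.3 and 62% v 92% at ICC 0.2 (chi-square v Kruskal-Wallis). Under the null, the split test rejects at or below about 5%.

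**2. Percent improvement, two arms, 40 v 65, SD 35**
- Chi-square on four nominal grades: about 50%.
- Rank test on the grades: about 68%.
- Rank test on the percentage: about 74%.

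Three-arm checks point the same way. Using grades, with odds ratios of 1/1/3, 1/1.7/3 and 1/1/4, power is 46% v 66%, 33% v 53% and 69% v 85% (chi-square v Kruskal-Wallis). With raw percentages (SD 30), chi-square on grades gives 42% v 72% for Kruskal-Wallis on the percentage (means 40/40/60) and 30% v 59% (means 40/50/60). Under the null, both tests on grades keep their size (4.1% and 4.7%).

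One illustrative table shows why. With rows 14/9/5/2, 8/9/9/4 and 4/8/12/6 (worst to best grade), chi-square = 10.77 on 6 degrees of freedom, p = 0.096, whatever the order of the columns. Kruskal-Wallis in the true order gives p = 0.006.

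**3. Residue rates**

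No limit is stated for residue above or within the rectosigmoid. A patient-level table therefore has no defined columns.

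**4. Conditional case: markers pooled over patients**

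This would treat 30 × 20 = 600 markers per arm as independent. The design effect is 1 + 19 × ICC, and the true size of a nominal 5% pairwise test is about 2 × [1 − Φ(1.96/√design effect)].
- ICC 0.1: design effect 1 + 1.9 = 2.9; size about 25%.
- ICC 0.3: design effect 1 + 5.7 = 6.7; size about 45% (simulations gave 44% to 46%).

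Kruskal-Wallis on per-patient rates stays at about 5% at every ICC tried.

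**The case against.** A reader might infer that the GITT analysis is pseudo-replicated and would produce gross false positives. The article does not support this. It nowhere says that markers are pooled, it defines the rate per patient, and its 90% limit points to a normal/abnormal count of patients, at least for excretion. That test is valid. The inflated error rates in step 4 apply only under a reading that the text leaves open but does not state.

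A reader might also infer that neither analysis uses the baseline score. For percent improvement that is wrong: the measure, like the TCMSS reduction, is by nature relative to the pre-treatment score. What is absent is covariate adjustment, and that is a design choice.

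It can further be said that the four response grades are prespecified, that section 2.14 gives categorical variables to chi-square or Fisher, and that testing the grades in this way is coherent and keeps its size. All of this stands, but it does not answer the loss of order. These are also secondary outcomes of a declared exploratory trial with no power target, and the primary outcome already has a rank test.

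A journal article may leave the unit of count to the full protocol. However, the choice of chi-square is stated here, and it differs from how the same section treats HRAM measurements.

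**Conclusion.** The point holds as a loss of efficiency on secondary outcomes, together with an undefined analysis for the two residue rates. Under the assumed scenarios the loss is about 16 percentage points of power for excretion (6 to 21 over the range tried). For percent improvement it is about 18 points against a rank test on the grades (68 − 50) and 24 against a rank test on the percentage (74 − 50). These sizes rest on ICCs, means and SDs that the article does not give. The direction was the same in every scenario examined.

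No inflated type I error is established, and the primary comparison is unaffected. The change is worth making because it costs nothing and uses tests the plan already names.

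**What to change.** In section 2.14:
- Analyse each patient's excretion rate and two residue rates as one value per patient, with Wilcoxon (two groups) or Kruskal-Wallis (three groups).
- Test percent improvement on the symptom scale and the TCMSS, or their ordered grades, with the same rank tests.
- Keep the 90% normal/abnormal split and the four-grade tables as descriptive patient-level summaries, and state that patients, not markers, are counted.

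Analysis of covariance on the baseline value is an optional alternative. The cost is a change of wording; data, visits and software stay the same.

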**Table 3 T3:**
[figure not shown]
The component of Chinese herb powder.

Patients with dietary interventions should follow the above, while patients without dietary interventions will continue their previous dietary habits. The treatment period is 28 days. During the treatment period, record the daily diet and defecation diary. The diet diary will be designed using a semi-quantitative food frequency method, and the defecation diary will collect information about the feeling of defecation, the shape of feces, and the time of each bowel movement. On the 14th day, the patient will be followed up by phone to know the status of the treatment process, and calculate the average number of complete spontaneous bowel movements (CSBMs) per week for the first 14 days, the average score of constipation symptoms and TCM syndrome. After 28 days of treatment, a second follow-up visit will be conducted to understand the condition of constipation (same as the first follow-up visit), and the patient will be required to complete the examination (48 hours gastrointestinal transit Time [GITT], high-resolution anorectal manometry [HRAM], blood routine [BR], liver and kidney function [LKF]). The short-chain fatty acids of the patient 's fresh stool (<30 min) should also be checked and the diary should be retrieved. During the intervention, patients will keep in touch with the researchers. The patient's diet and stool diary will be filled out by the doctor. Keep in touch with each patient in the treatment period through mobile phone software (WeChat), ask the patient to send 3 meals to the doctor's mobile phone, ask the patient about the stool on the day at 7 o’clock every night, and urge patients in the diet intervention group to insist on light vegetarian diet.

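### LOCF is the only missing-data method and can carry the baseline value to day 28, which biases the arm contrasts on CSBM per week even when dropout is completely at random

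*Protocol article*

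**What the plan says.** Section 2.14 (Planned statistical analysis) settles two things. On who is analysed: "all data of the patients randomized and at least 1 assessment (include baseline assessment) will be analyzed". On missing values, for patients who drop out or are terminated: "their missing data will be obtained by last-observation-carried-forward method". The article names no other imputation method and no missing-data sensitivity analysis. A per-protocol principle is mentioned beside intention to treat, but it does not say what happens to missing values.

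Other sections determine what the last observation can be:

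- Section 2.2: after enrolment, symptoms and bowel movements are recorded "on day 14 (phone follow-up) and day 28".
- Section 2.7: "The treatment period is 28 days". The day-14 call yields the average weekly CSBM count for the first 14 days. The same section adds: "During the treatment period, record the daily diet and defecation diary". Staff also ask each patient about that day's stool every evening.
- Section 2.11.2: "The number of CSBM per week is the primary outcome", with the responder rule: "It is effective when the number before the intervention subtracted from the number after the intervention is more than or equal to 1".
- Section 2.11.3: faecal short-chain fatty acids are sampled only before and after the intervention.

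**The concern.** LOCF assumes that nothing changes after a patient leaves. This trial exists to measure change over 28 days, so the assumption conflicts with its purpose. Admitting baseline-only patients makes this worse, because the carried value can be the baseline itself. Three consequences follow from the stated rules:

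- A patient who leaves before day 14 can have a change of zero, and so cannot meet the rule of an increase of at least 1.
- A patient who leaves after day 14 can have the first-half average stand in for day 28.
- For faecal short-chain fatty acids, only the baseline can be carried.

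Each arm's mean gain is then pulled toward zero in proportion to its dropout. The contrast between arms depends on how many patients left and when, as well as on what the treatments did. The Discussion says that a larger multicentre trial should be designed on the basis of this study, so a distorted contrast would feed into that design.

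**Working it through.** **The plan's own figures.** The article gives no effect size, standard deviation, power or dropout rate. The only arithmetic to reproduce is 3 arms × 30 = 90, which agrees. All rates and gains below are assumptions.

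**Step 1: formulas.** Let g be an arm's true mean gain in CSBM per week and d its dropout proportion, with dropout completely at random within the arm.

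- All dropouts carry baseline: LOCF mean gain = g × (1 − d).
- Half carry baseline, and half leave after day 14 with half the gain: LOCF mean gain = g × (1 − d + d × 0.5 × 0.5) = g × (1 − 0.75d).

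**Step 2: a true difference of 1.0** (gain 2.0 in the better arm, 1.0 in the other).

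| Dropout, better / other | All to baseline | Half leave after day 14 |
|---|---|---|
| 20% / 20% | 2.0 × 0.80 − 1.0 × 0.80 = 0.80 | 2.0 × 0.85 − 1.0 × 0.85 = 0.85 |
| 20% / 5% | 2.0 × 0.80 − 1.0 × 0.95 = 0.65 | 2.0 × 0.85 − 1.0 × 0.9625 = 0.74 |
| 5% / 20% | 2.0 × 0.95 − 1.0 × 0.80 = 1.10 | 2.0 × 0.9625 − 1.0 × 0.85 = 1.08 |

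Equal dropout shrinks the difference by 15% to 20%. Unequal dropout moves it by about −35% to +10%, depending on direction and timing. Light dropout does little: 5% in both arms, all to baseline, gives 0.95.

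**Step 3: no true difference.** If all dropouts carry baseline, the false contrast is g × (difference in dropout). With 10% against 30% dropout and a common gain of 1 to 2, it is 0.2 to 0.4 CSBM per week. With equal dropout it is zero.

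**Step 4: responder rule.** A carried baseline cannot be a response, so the observed rate is p × (1 − d). With a common true rate of 40% to 60% and 10% against 30% dropout, the false difference is 0.20 × p, or 8 to 12 percentage points.

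**Step 5: simulation with no true difference** (30 per arm, two arms, 6,000 runs). Assumed: baseline mean 1, gains of 1 by day 14 and 2 by day 28, SD 1.2, correlation 0.5, values floored at 0, dropout completely at random within arm, two-sided z test at 0.05.

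| Dropout | Leaving before day 14 | LOCF mean contrast | LOCF rejection | Completers' rejection |
|---|---|---|---|---|
| 20% / 20% | half | 0.01 | 5% | 5% |
| 10% / 30% | half | −0.29 | 16% | 5% |
| 10% / 30% | all | −0.38 | 23% | 6% |
| 5% / 35% | all | −0.56 | 43% | 5% |

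**Step 6: standard errors.** At 10% / 30% the LOCF standard error was 0.313 (half leaving early) or 0.320 (all), against 0.328 for completers. The ratios are 0.313/0.328 = 0.95 and 0.320/0.328 = 0.98, so LOCF is about 2% to 5% lower. It also lay close to the estimator's own sampling spread (0.317 and 0.320). The problem is the centre of the interval much more than its width.

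**The case against.** Several counter-arguments have force.

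- **Unequal dropout is not documented.** A reader might infer from the Discussion that the diet arms will lose more patients. That text says practical factors will hinder the diet, which is adherence, measured separately by the dietary compliance rate (section 2.11.5). A non-adherent patient who stays has no missing outcome, and sections 2.4 and 2.7 describe active retention. This stands. Unequal dropout is a plausible risk, mainly for A against B or C. B and C share the same open diet and differ only in blinded powder, so the diet gives no reason for unequal dropout between them. Step 2 shows, however, that equal dropout already shrinks a real difference.
- **Not every dropout reverts to baseline.** A day-14 value exists for later leavers. This stands, and is why ranges are given.
- **LOCF makes standard errors badly wrong.** This stronger reading is tempting because filled values count as observed. Under the assumptions used, the effect is minor.
- **LOCF discards the diary.** The article does not say whether visit averages or diary entries are carried forward, so this cannot be asserted.
- **A return to baseline might be the intended value after stopping.** The Discussion says that constipation can recur once existing medicines are stopped. A composite outcome built on that could be defended, but the article defines none.
- **The planned primary test is rank-based and the study is exploratory.** The figures above are for means, so they do not give the size of the error in the rank test. Zeros inserted at different rates shift ranks as well. The exploratory aim lowers the stakes without removing the bias.

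**Conclusion.** The point holds. As written, section 2.14 makes LOCF the sole method and allows baseline to be carried to day 28, and nothing else in the article corrects this. It is a stated choice, so it cannot be put down to a detail left to an unseen analysis plan.

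Bias arises even when dropout is completely at random, provided the outcome changes over time and either the true gains or the dropout rates differ between arms. If both are equal, with the same timing of change and dropout, the mean contrast stays at zero. Its direction is not fixed: under the assumed inputs a true difference of 1.0 is estimated at anything from 0.65 to 1.10. These values illustrate the mechanism. They do not predict this trial's error, since neither dropout nor effect is stated.

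**What to change.** In section 2.14, make the primary analysis a likelihood-based longitudinal model of CSBM per week with three periods (baseline, days 1–14, days 15–28) and an arm-by-time term. Include every randomised patient and use the diary data observed up to dropout. Keep the planned rank test and LOCF as sensitivity analyses.

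Derive the comparison on the rule of an increase of at least 1 from multiple imputation. Counting missing as non-response would not cure the problem: for early leavers it gives the same p × (1 − d) as a carried baseline.

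No new visits or data are needed. The cost is a little more analysis work and a change of primary method, which is more than a wording edit and should be made before unblinding. The model assumes data are missing at random, and a delta-adjusted sensitivity analysis can check how far the conclusion depends on that.
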